### Calculation of required sample size

Using Stata statistical software to model an ANCOVA analysis of the primary outcome at six months, with power of 80% and alpha level of 5%, we estimate that 14 participants will be required per group, i.e. 28 in total. To account for dropouts, we aim to recruit up to 32 participants into the study. The effect size was estimated as a weight difference of 5 kg at 6 months between the groups, 74 kg (SD 9 kg) in the standard group and 69 kg (SD 12 kg) in the intervention group. These estimates reflect data from a non-randomised study of intensive nutrition interventions versus standard care in a comparable population of kidney transplant recipients whose weights were similar at baseline [49]. The correlation between weight at baseline and 6 months was estimated as 0.9, based on data showing a mean difference in weight of 3.2 kg (SD 5.9 kg) between 1 and 6 months of 1299 kidney transplant recipients who received their kidney transplant in Auckland between 1991 and 2012 (unpublished observations, data on file), where the correlation was 0.9514. Similar findings were found in an analysis of weight change post-transplant in a comparable population of 156 transplant recipients in Brisbane, Australia (mean weight change 3.3 kg, SD 6.0 kg) ([name], personal communication) [18].

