Historical data from a non-randomised study of nutrition interventions in the early period post-transplant [49] have been used to estimate the effect of the intervention on weight change after transplant. More recent data are not available to provide a more reliable estimate of the likely effect size, and it is thus possible that there may be more variability in weight gain observed in this population, and hence a larger sample size may be required for the same power. Some protection, however, is afforded by the fact that the primary outcome analysis will be accomplished using ANCOVA, rather than a t-test on weight change as used in the Patel study [49]. Previous data on post-transplant weight change in our population shows a high degree of correlation between weight at baseline (one month) and six months, supporting the use of an ANCOVA [72].

Due to the nature of the intervention, it is not possible to blind participants or investigators involved in the intervention to group allocations, and thus there is a potential risk of bias. We have attempted to minimise this by using single-blind design, i.e. by having formal measurements of weight and other measures that will be reported as study outcomes performed by a blinded investigator. In addition, to reduce the potential for confounding due to measurement variability, a single investigator will perform all of the outcome measurements using the same instruments throughout the study.

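### The 80% power for 14 per group rests on an implied weight-change SD of 4.7 kg, while the same paragraph reports 5.9 and 6.0 kg; on those figures power for 5 kg is roughly 60%

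*Protocol article*

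**What the plan says.** All the inputs stand in one paragraph of the Protocol article, Calculation of required sample size.

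- Target: "The effect size was estimated as a weight difference of 5 kg at 6 months between the groups".
- Spread: "74 kg (SD 9 kg) in the standard group and 69 kg (SD 12 kg) in the intervention group". On the source, the paragraph says: "These estimates reflect data from a non-randomised study of intensive nutrition interventions versus standard care in a comparable population of kidney transplant recipients".
- Correlation: "The correlation between weight at baseline and 6 months was estimated as 0.9". The support given is "based on data showing a mean difference in weight of 3.2 kg (SD 5.9 kg) between 1 and 6 months of 1299 kidney transplant recipients", with an observed correlation of 0.9514. A second cohort, 156 recipients in Brisbane, is cited as similar, with a mean change of 3.3 kg and SD 6.0 kg.
- Result: "with power of 80% and alpha level of 5%, we estimate that 14 participants will be required per group, i.e. 28 in total", raised to as many as 32 to cover dropouts.

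Under Statistical analysis, the primary comparison is an ANCOVA of 6-month weight on group, baseline weight, baseline obesity and gender. The Discussion concedes that weight gain could vary more than assumed and that more participants might then be needed. It adds: "Some protection, however, is afforded by the fact that the primary outcome analysis will be accomplished using ANCOVA", in contrast with the change-score t test used in the cited study.

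**The concern.** The precision of an ANCOVA on weight is set by the residual SD after baseline weight is taken out. That residual depends on the outcome SD and the correlation jointly. A correlation observed in a cohort with widely spread weights need not carry over to a sample with much less spread. If it is carried over unchanged, the implied within-person variation shrinks with the spread.

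Here the correlation comes from the local cohort and the spread from another study. The figure that would tie the two together, the local SD of weight change, is printed beside them but not used.

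At stake is the meaning of the primary result. A non-significant finding from 28 to 32 participants would be read against a stated 20% risk of missing a true 5 kg difference. On the paragraph's own local figures that risk is about 40%.

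**Working it through.** **1. Reproduce the plan's figure.** Two-sided alpha 0.05 (sidedness is not stated, but two-sided reproduces the result), power 80%, difference 5 kg, SDs 9 and 12 kg, r = 0.9:

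n per group = (1.96 + 0.8416)² × (9² + 12²) × (1 − 0.9²) / 5² = 7.849 × 225 × 0.19 / 25 = 13.42, rounded up to 14.

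Other readings do not give 14: one-sided gives 11, ANCOVA with r = 0.9514 gives 7, and a change-score test with r = 0.9 gives 14.13, so 15. With no baseline adjustment the number is 71.

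**2. What these inputs imply.**

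- Pooled SD = √((81 + 144)/2) = 10.61 kg.
- SD of change = 10.61 × √(2 × (1 − 0.9)) = 4.74 kg.
- ANCOVA residual SD = 10.61 × √(1 − 0.81) = 4.62 kg.
- Power at 14 per group = 82% by the normal formula, or 78% by noncentral t with 28 − 5 = 23 df.

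The paragraph itself reports change SDs of 5.9 and 6.0 kg, not 4.74 kg.

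**3. Residual SD from the local data.** The local weight SDs are not given. *Assumption: equal weight SDs at 1 and 6 months.* Then weight SD = SD of change / √(2(1 − r)), and residual SD = SD of change × √((1 + r)/2).

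For Auckland (5.9 kg, r = 0.9514), weight SD = 5.9 / √0.0972 = 18.9 kg, against the 9 and 12 kg used. Residual SD = 5.9 × √0.9757 = 5.83 kg.

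**4. Power for 5 kg on the local change SDs.**

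| SD of change, r | Residual SD | 14 per group, normal | 14 per group, t (23 df) | 16 per group, t (27 df) |
|---|---|---|---|---|
| 5.9, 0.9 | 5.75 kg | 63.3% | 59.6% | 66.0% |
| 5.9, 0.9514 | 5.83 kg | 62.2% | 58.5% | 64.8% |
| 6.0, 0.9 | 5.85 kg | 61.9% | 58.2% | 64.5% |
| 6.0, 0.9514 | 5.93 kg | 60.7% | 57.1% | 63.3% |
| Plan's inputs | 4.62 kg | 81.6% | 78.2% | – |

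The 16-per-group column is the case in which all 32 are retained.

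**5. Detectable difference at 80% power, 14 per group.** Normal: 2.8016 × residual SD × √(2/14), which is 6.09 kg at 5.75 and 6.28 kg at 5.93. By noncentral t with 23 df: 6.36 to 6.55 kg.

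**6. Sensitivity to the equal-SD assumption.** With change SD 5.9 kg, r = 0.9514 and a 6-month to 1-month SD ratio k, the 1-month SD is 5.9 / √(1 + k² − 2rk) and the residual SD is k × that SD × √(1 − r²). For k from 0.9 to 1.2 the residual SD lies between 5.24 and 5.90 kg, and t-based power (25 df) between 58% and 68%.

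**7. What other covariates would have to do.** To bring 5.83 kg back to 4.62 kg, they must remove 1 − (4.62/5.83)² = 37% of the variance left after baseline weight.

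**8. ANCOVA against a change-score test.** On the plan's inputs, 13.42 v 14.13 per group. On the Auckland data, residual SD 5.83 kg v change SD 5.9 kg.

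**The case against.** Several points on the other side are fair.

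- *The sum is right.* The 14 follows from the inputs given, so a reader who inferred a calculation error would be wrong. Taking an effect and SDs from one study and a correlation from another is common, and rounding 0.9514 down to 0.9 is conservative in itself. What stands is that the combination conflicts with a figure printed beside it.
- *The risk is disclosed.* A reader might infer that the Discussion conceals the problem. It does not: it says variability may be greater and a larger sample may be needed. What it omits is that the local data already show the greater variability. Its remark on ANCOVA is a comparison with a change-score test only. Against that test the gain is small but real, so the remark is weak rather than false, and the drop from 71 to 14 per group does not refute it.
- *The local cohort is not the trial population.* It covers transplants from 1991 to 2012. The trial sets BMI limits of 18.5 and 40 kg/m², requires stable graft function, uses a single assessor with the same instruments, and adjusts for obesity and gender. Each could reduce the residual variance. The article quantifies none of this, so it can be credited neither as a full rescue nor as nothing.
- *Like must be compared with like.* Setting the t-based 57-60% against the stated 80% overstates the gap, since the plan's own inputs give 78% on that basis. The matching pairs are 61-63% v 82% (normal) and 57-60% v 78% (t).

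**Conclusion.** The point holds. The stated 80% power depends on a residual SD of 4.62 kg that the local data in the same paragraph do not support. With change SDs of 5.9-6.0 kg, r of 0.9-0.9514 and equal weight SDs at the two times, the loss is about 20 percentage points on either method. Keeping all 32 participants does not close the gap.

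It would be too strong to read any of these figures as the trial's actual power. The equal-SD assumption cannot be checked from the article, and the value of the extra covariates and eligibility limits is unknown. An ANCOVA residual SD also cannot exceed the SD of change, so the equal-SD values sit close to their ceiling and the power figures close to their floor. Over the SD ratios examined, however, power stays below 80%. Nor do the documents show that the trial must recruit more; what has to change is the statement of what 28 evaluable participants can detect.

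**What to change.** In Calculation of required sample size, redo the calculation from the local SD of change and declare the equal-SD assumption. State that 28 evaluable participants give roughly 60% power for 5 kg, or 80% power for about 6.1-6.3 kg (normal formula) or 6.4-6.6 kg (noncentral t), naming the method used. If the team expects obesity, gender or the eligibility limits to lower the residual variance, give the expected reduction and its source.

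In the Discussion, replace the suggestion that variability might prove larger with a statement that the local data already show it. Add that the ANCOVA gain is already counted in the 14 per group and is small relative to a change-score test.

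The cost is rewording two paragraphs and accepting a less favourable stated power. No extra patients are needed, and neither the design nor the analysis changes.

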### Statistical analysis

The primary outcome (body weight at 6 months post-transplant) will be compared between the groups using an analysis of covariance (ANCOVA) adjusted for baseline weight, baseline obesity (BMI ≥ 30 kg/m^2^), and gender. The extent of weight gain after transplant has been shown be significantly affected by baseline BMI [18]; gender will be included as a covariate due to its use as a stratification variable in the randomisation.

Secondary analyses will include analyses of change in anthropometry (BMI, waist circumference, and waist-hip ratio), physical function, body composition, quality of life, and biochemistry parameters between the groups, using ANCOVA with adjustment for relevant baseline covariates. Repeated measures analyses using linear mixed models with multiple covariates will be used to compare changes in weight, anthropometry, physical function, body composition, quality of life, and biochemistry parameters over time (baseline, 3, 6 and 12 months) between the groups. Multiple linear regression will be used to identify significant predictors other than group allocation associated with these changes. Variables identified as significant will be analysed with pairwise comparisons.

Comparisons between groups for differences in variables of interest will be conducted using Fisher’s exact test for categorical variables, unpaired t tests for parametric variables, and Wilcoxon rank sum tests for non-parametric variables.

All statistical analyses will be performed using appropriate statistical software, such as STATA or SAS. The level of statistical significance will be set at probability level of <0.05.

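### The stated 80% power with 14 per group is a large-sample, single-covariate figure; the planned three-covariate ANCOVA in 28 people has about 75–78% on the same inputs

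*Protocol article*

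**What the plan says.** The section on calculation of required sample size describes an ANCOVA model of 6-month weight and states: "with power of 80% and alpha level of 5%, we estimate that 14 participants will be required per group", 28 in total. Its inputs are:

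- Difference: "The effect size was estimated as a weight difference of 5 kg at 6 months between the groups".
- Means and SDs: "74 kg (SD 9 kg) in the standard group and 69 kg (SD 12 kg) in the intervention group".
- Correlation: "The correlation between weight at baseline and 6 months was estimated as 0.9". The local data behind this choice are described in the same sentence, "where the correlation was 0.9514".
- Attrition: "To account for dropouts, we aim to recruit up to 32 participants into the study".

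The Statistical analysis section fixes the primary model as an ANCOVA "adjusted for baseline weight, baseline obesity (BMI ≥ 30 kg/m^2^), and gender". The section on recruitment, randomisation and blinding gives 1:1 allocation, stratified by gender.

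**The concern.** The sample size inputs describe one covariate, baseline weight. The planned model has three, plus the group term and the intercept. In 28 people two costs follow that a large-sample formula leaves out. The test uses a t distribution with few degrees of freedom. Chance differences between the arms in baseline weight and obesity also widen the standard error of the adjusted treatment effect. If neither cost is counted, the trial carries a power claim that its own analysis does not meet even when the stated difference, SDs and correlation are right. A null result would then be read against a somewhat overstated power. The four extra recruits would also be partly needed to reach the target, although the protocol assigns them to dropout.

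**Working it through.** **Inputs (protocol article, sample size section).** Difference 5 kg; SDs 9 and 12 kg; r = 0.9; alpha 5%; power 80%; 14 per group. Sidedness is not stated.

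**1. Reproduce the stated figure.**
- Pooled variance = (81 + 144)/2 = 112.5, so SD = 10.61 kg.
- Residual variance after baseline weight = 112.5 × (1 − 0.81) = 21.375, so residual SD = 4.62 kg.
- n per group = 2 × 21.375 × (1.960 + 0.842)² / 5² = 2 × 21.375 × 7.849 / 25 = 13.42, rounded up to 14.
- Normal-approximation power at 14: SE = √(2 × 21.375/14) = 1.747; 5/1.747 = 2.861; power = Φ(2.861 − 1.960) = 81.6%.

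The other readings tried do not give 14: one-sided gives 11, no covariate adjustment gives 71, and r = 0.9514 with the same SDs gives 7.

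**2. Use the t distribution for the planned model, with covariates perfectly balanced.** Parameters: intercept, group, baseline weight, obesity, gender. Residual df = 28 − 5 = 23; critical t = 2.069; noncentrality 2.861. Power = 78.2%. With baseline weight as the only covariate (25 df) it is 78.5%, so most of the loss here comes from replacing the normal by the t distribution.

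**3. Add expected chance imbalance.** For k covariates not balanced by design, the variance of the treatment contrast is inflated on average by 1 + k/(2n − k − 3). Gender is balanced by stratification, so k = 2 (weight and obesity): 1 + 2/23 = 1.087. The SE becomes 1.747 × √1.087 = 1.822, the noncentrality 5/1.822 = 2.744, and power with 23 df = 74.8%.

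**4. Simulation cross-check.** The planned model was simulated (15,000 runs per scenario) with gender balanced. The obesity indicator was generated from baseline weight and an assumed height distribution, with a 50:50 gender split and a common baseline mean of 71 kg. None of these three is in the protocol. Power at 14 per group was 75.1% with SDs of 9 and 12, and 74.7% with equal SDs.

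**5. How many analysed participants give 80%?** Same inputs, three-covariate model:

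| Analysed per group | Covariates balanced | Imbalance in weight and obesity |
|---|---|---|
| 14 | 78.2% | 74.8% |
| 15 | 81.2% | 78.2% |
| 16 | 83.9% | 81.2% |

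Simulation at 16 per group with equal SDs gave 81.4%. The target is therefore met at 15 per group in the best case and at 16 with chance imbalance.

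**The case against.** **The stated number is not a slip.** Fourteen is what the usual large-sample ANCOVA formula gives, and that formula is in common use. This stands: a reader might infer an arithmetic error, but the figure reproduces. The point is a mismatch between the formula and the analysis.

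**The extra covariates may earn their keep.** Obesity is included because baseline BMI is said to affect weight gain. If obesity and gender removed about 4% of the residual variance (balanced case) or about 12% (imbalance in weight and obesity), power would return to 80%. This stands as a limit on the result. The protocol neither claims nor quantifies such a gain, and obesity is itself partly derived from baseline weight.

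**The correlation was rounded down.** With the same SDs, r of about 0.905 to 0.913 restores 80%, and 0.9514 gives 96–97%. However, 0.9514 comes from data with a change SD of 5.9 kg. If the SD is the same at both times, these imply an SD of 5.9/√(2 × 0.0486) = 18.9 kg and a residual SD of 18.9 × √(1 − 0.9514²) = 5.8 kg, which is larger than the 4.62 kg used. Taking that correlation with the smaller SDs mixes two sources. Which SD is right is a separate question, and the present point does not rely on it.

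**The Discussion already warns that more participants may be needed.** That caveat concerns greater variability in weight gain. It does not cover degrees of freedom or covariate imbalance when the inputs are correct.

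**Stronger readings that do not hold.** A reader might put power at 73% and the requirement at 17 per group. Those figures charge imbalance for all three covariates and so ignore the stratification by gender. A reader might also say that no dropout allowance remains. That goes too far: 30 completers still give 78–81%.

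**Conclusion.** The point holds at a modest size. The protocol's 80% is a large-sample, single-covariate figure. The analysis it specifies falls about 2 points short in the best case and about 5 points short once expected chance imbalance in weight and obesity is allowed for. This rests on the stated difference, SDs and r = 0.9, a two-sided 5% test, equal arms, gender balanced by stratification, and no variance explained by obesity or gender beyond baseline weight. The design is not invalidated. What needs correcting is the stated power and the account of what the extra four recruits cover.

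**What to change.** Restate the power in the sample size section, on the t distribution and with the full covariate set. For example: *With 28 analysed participants the planned ANCOVA has about 75–78% power for a 5 kg difference under these inputs; 80% needs about 15–16 analysed per group. The range runs from expected chance imbalance in baseline weight and obesity to perfect balance, with gender balanced by stratification, and assumes that obesity and gender explain no variance beyond baseline weight.* Add that 32 recruits give about 81–84% only if all complete, so the dropout allowance is largely used by the analysis itself.

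The cost is a few sentences and a slightly less favourable stated power. Correcting the statement needs no extra patients and no change to the analysis.

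### The sample-size inputs imply a weight-change SD of 4.74 kg, but the same paragraph reports 5.9 and 6.0 kg; on the local figures, 14 per group gives roughly 60-70% power for 5 kg, not 80%

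*Protocol article*

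**What the plan says.** All the inputs are in the protocol article, under Calculation of required sample size.

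- Target: an ANCOVA of 6-month weight "with power of 80% and alpha level of 5" per cent, leading to "14 participants will be required per group, i.e. 28 in total", with up to 32 recruited to allow for dropout.
- Effect: "The effect size was estimated as a weight difference of 5 kg at 6 months between the groups", with means and SDs of "74 kg (SD 9 kg) in the standard group and 69 kg (SD 12 kg) in the intervention group".
- Source of the effect and SDs: "These estimates reflect data from a non-randomised study of intensive nutrition interventions versus standard care in a comparable population of kidney transplant recipients".
- Correlation: 0.9, supported by a "mean difference in weight of 3.2 kg (SD 5.9 kg) between 1 and 6 months of 1299 kidney transplant recipients" in Auckland, "where the correlation was 0.9514".
- A second cohort of 156 recipients in Brisbane is cited as similar, with a change SD of 6.0 kg.

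The Discussion adds that "it is thus possible that there may be more variability in weight gain observed in this population", so that more participants might be needed for the same power. It then says that using ANCOVA gives some protection.

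**The concern.** ANCOVA power depends on the residual SD of 6-month weight given baseline weight. That residual depends jointly on the spread of weights and on the correlation. A correlation reflects the spread of weights in the population it was measured in: for the same within-person change, a more widely spread population shows a higher correlation. Taking the SDs from one study and the correlation from another cohort can therefore produce a residual SD that matches neither.

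Here the change SDs are cited only to support the correlation. They are never compared with the change SD that the planning inputs imply. If the local figures are nearer the truth, the trial's stated power for its primary outcome is too high, and a null result could be taken as stronger evidence against a 5 kg effect than the design can give.

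**Working it through.** **1. Reproduce the stated figure.** Inputs: SDs 9 and 12 kg, r = 0.9, difference 5 kg, power 80%, alpha 5%. Sidedness is not stated; two-sided reproduces 14, one-sided would give 11. The usual large-sample ANCOVA formula gives

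n per group = (1.960 + 0.842)² × (9² + 12²) × (1 − 0.9²) / 5² = 7.849 × 225 × 0.19 / 25 = 13.42, rounded up to 14.

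**2. What the planning inputs imply.**

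- Pooled SD = √((81 + 144)/2) = 10.61 kg
- Residual SD = 10.61 × √(1 − 0.81) = 4.62 kg
- Change SD (equal SDs at both visits) = 10.61 × √(2 × 0.1) = 4.74 kg

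**3. What the Auckland figures imply.** With change SD 5.9 kg, r = 0.9514 and equal SDs at 1 and 6 months:

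- Weight SD = 5.9 / √(2 × (1 − 0.9514)) = 18.9 kg
- Residual SD = 18.9 × √(1 − 0.9514²) = 5.83 kg

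The like-for-like comparisons are:

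| Quantity | Planning inputs | Auckland figures |
|---|---|---|
| Change SD | 4.74 kg | 5.9 kg |
| Residual SD | 4.62 kg | 5.83 kg |

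The residual variance ratio is 5.83² / 4.62² = 1.59. If the SDs of 9 and 12 kg are kept instead, a change SD of 5.9 kg requires r = 1 − 5.9²/225 = 0.845, not 0.9.

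**4. Power for 5 kg with 14 per group, and detectable difference.** Normal-approximation power uses 5 / (residual SD × √(2/14)) − 1.960. The t-based column uses the noncentral t with 23 degrees of freedom (28 less intercept, group and three covariates). The detectable difference at 80% power is 2.802 × residual SD × √(2/14).

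| Inputs | Residual SD | Power, normal | Power, t | Detectable |
|---|---|---|---|---|
| As planned | 4.62 | 82% | 78% | 4.9 kg |
| Change SD 5.9, r = 0.9514, equal SDs | 5.83 | 62% | 58% | 6.2 kg |
| Change SD 5.9, r = 0.9, equal SDs | 5.75 | 63% | 60% | 6.1 kg |
| SDs 9/12 kept, r = 0.845 | 5.67 | 65% | 61% | 6.0 kg |
| Change SD 5.9, r = 0.9514, SD ratio 0.9 | 5.24 | 71% | 68% | 5.5 kg |
| Change SD 5.9, r = 0.9514, SD ratio 1.05 | 5.90 | 61% | 57% | 6.25 kg |

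The SD ratio is 6-month over 1-month. Between 0.9 and 1.2 the residual SD stays within 5.2-5.9 kg; it peaks near 1.05 and falls to 5.51 kg at 1.2. The Brisbane change SD of 6.0 kg, with r = 0.9514 and equal SDs, gives 61% (57% t-based).

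**5. If nobody drops out.** With 16 per group and residual SD 5.83 kg, power is 68% (65% t-based).

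**6. How much would have to be explained away.** By the normal approximation, 80% power at 14 per group needs a residual SD of 5 / (2.802 × √(2/14)) = 4.72 kg. From 5.83 kg that is a reduction in residual variance of 1 − (4.72/5.83)² = 34%; from 5.24 kg it is 19%.

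**7. The ANCOVA protection.** ANCOVA is already in the formula in step 1. Its gain over a change-score analysis is also small at the Auckland correlation: with equal SDs the variance ratio is (1 + 0.9514)/2 = 0.976, a saving of about 2%.

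**The case against.** Several points on the other side have force.

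- **The calculation is not wrong as arithmetic.** This stands. Someone who sees 62% beside 80% might infer a computing error, but 14 follows exactly from the stated inputs.
- **A single power figure is too precise.** This stands. The section gives no weight SD for Auckland at either visit, so 62% and 6.2 kg rest on an equal-SD assumption. A range is the honest form. About 80% returns only if the SD shrinks by some 15% between visits (ratio 0.85: residual 4.76 kg, power 79%). Nothing in the article suggests that, and mean weight rises by 3.2 kg over the period.
- **The Auckland cohort is not the trial population.** This partly stands. The cohort spans transplants from 1991 to 2012 with no selection described. The trial excludes BMI above 40 or below 18.5, requires stable graft function, uses one assessor and fixed equipment, and adjusts for obesity and gender. These features may well lower the residual SD, but no figure in the article supports the 19-34% reduction in variance needed. The local data are the best evidence offered, not proof of what the trial will see.
- **The correlation was discounted.** This is true: with SDs of 9 and 12 kg, r = 0.9514 would have given 6.70, or 7 per group, so using 0.9 doubled the number. The discount was real but incomplete, since 0.845 is the value that matches the change SD.
- **The Discussion already discloses the risk.** It does so in part. It calls greater variability possible, without noting that the sample-size section already reports a change SD larger than the planning inputs imply. It is not shown that the external study itself had a smaller change SD: that study's change SD is not given, and 4.74 kg is an implied value.

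**Conclusion.** The concern holds as an inconsistency in planning assumptions. The paired SDs and correlation imply a change SD of 4.74 kg, while the two cohorts cited beside them show 5.9 and 6.0 kg. On inputs consistent with the Auckland change SD, 14 per group gives about 62% power for 5 kg. The range is about 61-71% by normal approximation and about 57-68% t-based, for 6-month to 1-month SD ratios of 0.9 to 1.2. The difference detectable with 80% power is about 6 kg (5.5-6.25 kg). These figures assume that the Auckland change SD and correlation carry over to the trial and that the further covariates and eligibility limits remove no additional variance.

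A reader might go further and set the planned residual SD of 4.62 kg directly against the change SD of 5.9 kg, treat 62% as established, or conclude that the trial must be enlarged. The documents support none of these. The first compares unlike quantities. The second depends on SDs that the article does not report. The third does not follow, because the inconsistency bears on the power claim and leaves the analysis and type I error untouched.

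**What to change.** Keep the sample size.

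1. In Calculation of required sample size, base the power statement on one internally consistent source and drop the pairing of SDs 9/12 kg with r = 0.9. Suggested wording: *Using the Auckland change SD of 5.9 kg and correlation of 0.9514, and assuming equal weight SDs at 1 and 6 months, the residual SD is about 5.8 kg. With 14 per group the trial has roughly 60-70% power for a 5 kg difference, or 80% power for a difference of about 6 kg, allowing for moderate departures from equal SDs. The BMI limits and adjustment for obesity and gender may lower the residual SD by an unknown amount.*
2. If the sponsor holds the Auckland weight SDs at 1 and 6 months, use them in place of the equal-SD assumption and narrow the range.
3. In the Discussion, state that local data already show a larger change SD than the planning inputs imply, and remove the credit to ANCOVA as further protection, since it is already in the calculation.

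The cost is a few sentences and a less favourable power statement. No participants are added, and neither the design nor the analysis changes.
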